**Patient/ user group involvement**

Members of M-Alliance will be on our project advisory group and contribute to the interpretation, reporting and dissemination of the research. The M-Alliance is a user led organization which provides advocacy, training and helpline services to those currently in drug or alcohol treatment, those who have accessed treatment in the past and those who may access treatment in the future (http://www.m-alliance.org.uk/index.html). The M-Alliance has an ongoing interest in improving access to effective drug treatment, especially opiate substitution treatment (OST), for those that would benefit from treatment. Key policy statements recently by the M-Alliance have raised concern over the potential impact of shortening the duration of treatment (such as http://www.ukhra.org/putting_public_health_first/); and highlighted the importance of strengthening the evidence base on the benefits of treatment. Our previous analyses of the risk of drug related death during and after OST(11) were of interest and discussed with the M-Alliance who were keen to see these analyses extended and repeated. In particular there is a common interest in assessing the comparative effectiveness of methadone and buprenorphine – and sharing the findings with other users and drug workers. Financial support for members of the Alliance to participate in project meetings will be provided through the project grant. It is unlikely that M-Alliance participants will require training as we will be benefiting from their expertise, however, we will consult with NIHR PPI leads to provide advice at the beginning of the study. The Alliance will support research dissemination through summaries provided to their user fora, and through presentation to users and clinical practitioners at conferences such as the UK Harm Reduction Alliance conference on injecting.

**Limitations of the study design, data sources and analytic methods**

The key limitation is confounding – which we discuss and seek to address in our analysis plan above. Multiple analyses will be undertaken running the risk of “statistical multiplicity” and we will guard against over-interpretation of single statistical tests(42). The key hypothesis to be tested is whether there is evidence that buprenorphine is a safer substitution drug (in relation to mortality risk) than methadone. In addition, we will corroborate earlier analyses that hypothesised that mortality risk was elevated compared to other periods immediately after treatment cessation. Several analytic approaches will be presented in order to consider the extent of confounding and to aid interpretation of the analyses.

There are missing prescription data which may lead to misclassification of periods on and off (e.g. missing amount prescribed or daily dose in order to determine last date of prescription) – which we will subject to sensitivity analysis – including using different definitions/criteria for when a patient is on/off OST and using only the last prescription. Some patients maybe treated in specialist drug treatment clinics as well as primary care, which may introduce a potential bias if the information on other periods on OST is unrecorded. We will undertake analyses to estimate the frequency of this occurrence and how CPRD can be used to identify these periods. Periods in prison are unlikely to be recorded which also may introduce bias and confer additional risks (e.g. the period in prison will be at lower mortality risk but the period immediately following prison release is a period of high risk(43)). We can estimate the likely frequency and proportion of these events from other analyses to assess potential bias, and take these biases into account in the interpretation of our findings.

The analysis of CPRD will describe mortality risk for different periods on and off treatment for further mathematical models – which include other information – such as proportion of opiate dependent people in treatment. These also are subject to uncertainty and will be explored in sensitivity analyses.

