**Background**

Opiate substitution treatment (OST) is the key treatment for heroin dependence and has been shown to have multiple benefits, including reductions in drug related crime, blood borne virus transmission, and improvements in social functioning(1-5). Prescribed OST in the community includes methadone, buprenorphine, and dihydrocodeine(1, 6). There are approximately 200,000 people who inject drugs (PWID), half exposed to drug treatment annually, mainly OST (75%) but also non-pharmacological treatments delivered in specialist drug agencies and residential units. OST is effective because it reduces heroin injection and is cost effective because of reductions in drug related crime and health harms(7). Observational studies have shown that the risk of mortality is reduced during opiate substitute treatment(8-12). Buprenorphine has been shown to be as good as methadone at treatment retention(13), and hypothetically is less likely to cause fatal overdose than methadone(14). In France, ecological analyses suggest that trends in overdose deaths are negatively associated with increases in buprenorphine prescription(15). However, direct comparative evidence on the risk of death during buprenorphine vs. methadone is yet to emerge.

Several recent studies also have highlighted that there is a period of very high mortality risk (>8 times higher than mortality risk during treatment) in the first few months immediately after treatment cessation (9-11, 16). In the UK analyses of primary care information have suggested that the risk of death in those who receive OST is twice as high among men compared to women, and is raised at the beginning and end of treatment, and maybe higher in those co-prescribed benzodiazepines(11, 17). In Australia the risk of death at treatment onset was greater than in the UK, with some evidence to suggest that the mortality risk at treatment onset was lower among those initiated onto buprenorphine compared to methadone, but these benefits may be offset by a shorter duration of treatment for those on buprenorphine compared to methadone(9). The evidence base on other drug treatments (residential rehabilitation, detoxification, and psychological treatments) is more limited; but studies also suggest that the risk of mortality is reduced during treatment and elevated after treatment (10, 18).

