**Sample size/power calculation**

The main analysis is on opiate substation treatment (OST) in primary care and risk of death and in particular the comparison of methadone and buprenorphine*.

There will be at least 20,000 OST patients (extracted from CPRD GOLD patients) from 1998 to 2014 linked to NHS central registry and ONS mortality data, that will generate 67,000 person years (pys) follow-up (~32,000 on treatment and ~35,000 off) if censored 12 months after last OST. There will be over 700 deaths of which ~500 will be due to overdose. This will be the largest study in the UK with precise data on OST treatment exposure (including ~ 12000 pys on buprenorphine and 30,000pys on methadone). In addition, there will be approximately 10,000 and 12,000 person years in treatments lasting less than 1 month or greater than 12 months, and 3000 and 1200 person years follow-up in the first 4 weeks treatment on or immediately after methadone or buprenorphine treatment respectively.

Thus, there is sufficient power (> 90%) to determine whether:-

1. there is at least a halving of the risk of death during treatment on burpenorphine compared to methadone (i.e. 0.35% vs. 0.69% respectively) – which requires a sample of at least 922 in each group compared to 12,000 and 20,000 on buprenorophine and methadone
2. and sufficient power (80%) to test if the risk of death is at least a 1/3 lower on buprenorphine at (0.006%) compared to methadone (0.016%) in the first 4 weeks of treatment (1200 and 3000 person years respectively) – as indicated by unpublished analyses by Degenhardt on Australian mortality cohort(9).

In addition, there is sufficient power to corroborate that the risk of fatal overdose out of treatment at 0.8% is twice as high as the risk during treatment – which will require sample of at least 788 in and out of treatment compared to our sample of over 30,000 person years in each group; and that the risk of death in the 4 weeks after treatment at about 4.6% is 1/3 lower (3.0%) for people treated for short duration of treatment (< 1 month) compared to those treated for 12 months or longer – which will require sample of at least 3123 in each group compared to over 3500 and 3850 person years among those exposed to short or prolonged treatment respectively;

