**Use of linked data**

We will use link to ONS mortality file for our outcome measures. **Data/ Statistical Analysis Plan**

1) We expect that overdose and drug related mortality risk differs by period of treatment exposure (1-4 weeks treatment start, rest of treatment duration, 1-4 weeks treatment end, 5-52 weeks out of treatment). The main analysis will test whether there is evidence of a difference in mortality risk by modality of OST (methadone vs. buprenorphine) at different periods on and off treatment – and will investigate also mortality risk in relation to additional exposures (co-prescription of benzodiazepines, measures of treatment performance/quality) and confounders (age, gender, co-morbidity as defined by Charlson Index(24), alcohol and mental health problems, treatment episode number, calendar year) all of which have been shown to influence mortality risk(11) (9). However, other potential confounders or factors relating to injecting risk may be missing or incompletely measured in CRPD (such as crack-cocaine use).

We will undertake a series of analyses that aim to incorporate and adjust for confounding.

First, we will use Poisson regression incorporating time varying covariates (such as co-prescription of benzodiazepines, episode and duration of treatment) to describe mortality risks and compare these at different periods on and off treatment and by modality of OST. These analyses will generate incidence rate ratios (IRR) that compare mortality risk for patients on methadone (from week 4 to end of treatment as baseline) to other periods and other forms of OST; will compare mortality rate for key confounders (above); adjust IRR by period on or off treatment for these confounders; and examine specifically whether co-prescription of benzodiazpeines increases the risk of mortality during and after treatment.

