3) The estimates of the effect of different drug treatments on mortality risk for different periods on or off treatment derived from analyses of Clinical Practice Research Datalink (CPRD) and Drug Data Warehouse (DDW) will be used in differential equation or individual based models that consider the flow of people into and out of drug treatment fitted against estimates of the annual number of drug related deaths in the population. The models will incorporate treatment coverage and extend previous models(11) by including additional factors that may affect the risk of overdose death or duration maintained on treatment in this analysis. This will be decided through consultation with other researchers on the grant and key stakeholders (Public Health England, Bristol Health Integration Team on Addiction) and may include:- modality of treatment, combination of treatments, age, gender, treatment history, benzodiazepine prescription, alcohol abuse, other psychosocial and family therapy (if data on intervention effect are available). An individual based model will be used if it is deemed important to incorporate the full heterogeneity in treatment duration and/or if an individual’s past treatment episodes are shown to effect the duration that they remain on treatment or the mortality rate while on treatment. The model will be parameterized with data from this study, and key uncertainties will be varied in a Bayesian framework to obtain multiple possible model fits to the annual number of drug related deaths in the population at certain times points in the past(38). Model fits will be weighted by their goodness of fit using likelihood measures (39, 39).

The model fits for each time point will be used to firstly evaluate the impact of current and past levels of drug treatment on decreasing drug related deaths in the population (11, 22), with model fits being used to test hypotheses for why the yearly number of overdose deaths has not decreased over the last 10 years while the rate of methadone deaths per gram has decreased. The hypotheses will be incorporated into the model fitting process through assumptions made about the uncertainty ranges or values assumed for specific parameters, and then the likelihood of specific hypotheses will be evaluated through the relative degree to which the model fits the data with that parameter assumption(40, 41).

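### The main test of whether buprenorphine is safer compares the drugs within on/off-treatment periods, so any difference in retention between them is left out of the contrast

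*Protocol*

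**What the plan says.** **Hypothesis.** Limitations of the study design: "The key hypothesis to be tested is whether there is evidence that buprenorphine is a safer substitution drug" than methadone, with regard to mortality. The sentence does not say over what time, or from what starting point, safety is measured.

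**Main analysis.** Data/Statistical Analysis Plan, item 1 (printed directly after Use of linked data), tests for a "difference in mortality risk by modality of OST (methadone vs. buprenorphine) at different periods on and off treatment". The first method is "Poisson regression incorporating time varying covariates (such as co-prescription of benzodiazepines, episode and duration of treatment"). Its rate ratios "compare mortality risk for patients on methadone (from week 4 to end of treatment as baseline) to other periods and other forms of OST".

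**Power.** The first power statement is for whether "there is at least a halving of the risk of death during treatment on burpenorphine compared to methadone (i.e. 0.35% vs. 0.69% respectively"). The second concerns the first 4 weeks of treatment.

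**Retention.** The Background says two things. On an Australian cohort with some evidence of lower risk at treatment onset on buprenorphine, it says "these benefits may be offset by a shorter duration of treatment for those on buprenorphine compared to methadone". Earlier it says "Buprenorphine has been shown to be as good as methadone at treatment retention". It also puts mortality in the first months after cessation at more than 8 times the on-treatment level.

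**Other analyses.** The propensity-score analysis is to test for mortality differences between the two drug groups, and the marginal structural models weight by treatment history. Neither says whether its contrast is within period or from initiation. Item 3 describes a model of flow into and out of treatment. Its additional factors are to be settled by consultation and "may include:- modality of treatment, combination of treatments, age, gender, treatment history".

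**The concern.** A rate ratio within a period compares patients who are in that period now. It cannot register how soon a drug's patients leave treatment and enter the weeks after cessation, where the protocol expects the highest mortality. Including duration as a covariate takes out more of the same information.

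That is a valid answer to one question: which drug has the lower death rate while a patient is taking it, or at a given time after stopping it. A clinician or guideline group told that a drug is safer may instead understand that fewer of the patients started on it die. The two answers agree when retention is equal and can part when it is not. The protocol raises that possibility itself, and its objectives say that the results should inform treatment guidelines. Yet no analysis is committed to the second question, and the model that could join rates with durations lists modality only as optional.

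**Working it through.** **The plan's own figures.** The on-treatment ratio is 0.35/0.69 = 0.51. The stated requirement of 922 per group does not reproduce from these percentages: the usual two-proportion formula (90% power, two-sided 5%, an assumed level) gives 9,402, or 9,982 with continuity correction. With 12,000 and 20,000 treated as group sizes, power is about 98%, so the on-treatment contrast remains well powered as planned. The sample-size slip is a separate matter and does not affect this point.

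**Inputs, read as rates per 100 person-years.** From the sample size section:
- on treatment: 0.35 (buprenorphine), 0.69 (methadone);
- first 4 weeks after treatment: 4.6;
- later off treatment: 0.8, which is a fatal overdose figure; the others are deaths.

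Because 0.8 covers overdose only, a second value is tried: 2 × 0.69 = 1.38. It applies to all deaths the doubling that the protocol states for overdose, and is an assumption. Off-treatment rates are taken as equal for both drugs. The protocol gives no episode length by drug, so mean durations are assumed.

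**Formula.** One episode, exponential with mean m years, no restart, 12-month horizon, w = 4/52:
- time on treatment: A = m(1 − e^(−1/m))
- later off time: B = (1 − w) − m(1 − e^(−(1−w)/m))
- time in the 4 weeks after treatment: P = 1 − A − B
- deaths per 100 starters = on-rate × A + 4.6 × P + off-rate × B

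| Mean duration | A | P | B |
|---|---|---|---|
| 3 months | 0.2454 | 0.0753 | 0.6793 |
| 6 months | 0.4323 | 0.0657 | 0.5020 |
| 9 months | 0.5523 | 0.0556 | 0.3921 |
| 12 months | 0.6321 | 0.0475 | 0.3204 |

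**Worked example, 3 against 9 months, off-rate 0.8.**
- Buprenorphine: 0.35 × 0.2454 + 4.6 × 0.0753 + 0.8 × 0.6793 = 0.086 + 0.346 + 0.543 = 0.976 (from unrounded terms).
- Methadone: 0.69 × 0.5523 + 4.6 × 0.0556 + 0.8 × 0.3921 = 0.381 + 0.256 + 0.314 = 0.950 (from unrounded terms).
- Ratio 1.03.

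**Results.** Each cell is deaths per 100 starters, buprenorphine / methadone, and their ratio. The on-treatment ratio is 0.51 in every row.

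| Mean months, buprenorphine vs methadone | Off-rate 0.8 | Off-rate 1.38 |
|---|---|---|
| 6 vs 6 | 0.855 / 1.002 = 0.85 | 1.146 / 1.293 = 0.89 |
| 4 vs 6 | 0.933 / 1.002 = 0.93 | 1.288 / 1.293 = 1.00 |
| 6 vs 12 | 0.855 / 0.911 = 0.94 | 1.1462 / 1.0968 = 1.05 |
| 3 vs 9 | 0.976 / 0.950 = 1.03 | 1.370 / 1.178 = 1.16 |
| 3 vs 12 | 0.976 / 0.911 = 1.07 | 1.370 / 1.097 = 1.25 |

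**Break-even.** Mortality per starter is equal when mean buprenorphine duration is as follows:
- methadone mean 6 months: 2.4 months (39%) at off-rate 0.8, 3.9 months (66%) at 1.38;
- methadone mean 12 months: 4.5 months (38%) at off-rate 0.8, 6.8 months (57%) at 1.38.

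**Sensitivity to the post-treatment rate.** The sample size section posits 3.0% after treatment of under 1 month. Using 3.0 after those episodes and 4.6 after longer ones, with off-rate 0.8, gives 1.00 (3 vs 9), 1.04 (3 vs 12) and 0.93 (6 vs 12). With off-rate 1.38, 6 vs 12 gives 1.04.

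**The case against.** **Retention may be equal.** A reader might infer that buprenorphine is known to retain patients for less time and that the analysis hides this. The Background does not support that: the shorter-duration remark is hedged and tied to one Australian source, and the same section reports retention as good as with methadone. With equal durations nothing reverses. This stands in full.

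**Duration is not ignored.** Modality and duration of treatment are secondary outcomes. The objectives promise to relate effects to treatment coverage and duration, and the model projections are to cover combinations of modalities and changes in duration. Period-specific rates are the inputs such a model needs. This stands, but modality-specific input to the model remains optional, and no text links the conclusion on safety to the model's output.

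**Some analyses may already count from initiation.** A reader might infer that every test of the key hypothesis is within period. The text does not show that. Follow-up starts at the first prescription, and the propensity-score and marginal structural analyses state no conditioning on period. A separate analysis plan could define them that way. What remains is that the protocol does not commit them to it.

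**A wrong conclusion is not built in.** No rule says that a lower on-treatment rate alone means safer; off-treatment periods are compared too; and the Limitations section promises caution over single tests. This stands.

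**The arithmetic depends on chosen durations.** It does. It also leaves out raised risk early in treatment, where the protocol expects a buprenorphine advantage, and it leaves out repeat episodes.

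**Conclusion.** The point holds as a gap between the stated hypothesis and the main test of it. The main contrast leaves out any retention difference between the drugs, and nothing in the protocol commits another analysis to put it back by modality.

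Its size is unknown, because the protocol gives no durations by drug. In the illustration, equal retention still favours buprenorphine (0.85 at 6 months, off-rate 0.8), though by less than the on-treatment ratio of 0.51. With off-rate 0.8 the advantage is lost only if mean buprenorphine duration falls below about 38–39% of a methadone mean of 6 to 12 months; with 1.38, below about 57–66%. These figures assume single exponential episodes, equal off-treatment rates for both drugs, and a mixture of all-cause and overdose risks. They show that divergence is possible, not that it is expected.

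It would go too far to say that the period-specific analysis is wrong or should give way to one from initiation. Risk while exposed and the effect of starting a drug are both legitimate questions, and the protocol does not rule out answering both.

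**What to change.** 1. **Data/Statistical Analysis Plan, item 1:** add mortality over 12 months from the first prescription of a new episode, by starting drug. Count later time on, off and switched, and adjust with the planned propensity score. Report it beside the period-specific rate ratios.
2. **Item 3:** move modality-specific rates and durations from the optional list to the required model inputs.
3. **Limitations:** state that a lower period-specific rate will be interpreted together with the results of 1 and 2.

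The cost is one further analysis on data already being extracted, plus wording. Switching between drugs dilutes the contrast from initiation. Its precision may also be limited: the December 2015 amendment reports that the earlier linkage left analyses underpowered, and no power has been worked out for this contrast. It should therefore supplement the period-specific analysis, and agreement between the two should not be made a condition for any conclusion.

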**Study population**

Data extraction comprises all patients aged 16-64 who have been prescribed methadone, buprenorphine or dihydrocodeine in CPRD practices from 1997 to 2014. Patients solely prescribed dihydrocodeine will require additional evidence of drug addiction. This will include a sub-set of patients eligible for ONS linkage.

Patients prescribed methadone or buprenorphine will be identified from the following product codes.

Additional patients will be identified based upon prescriptions for dihydrocodeine using the following list of product codes

and evidence of drug addiction from the following list of medcodes.

The study population will be a subset of the data extraction based upon prescription dose and diagnoses to confirm that prescriptions were for opiate substitution treatment (OST) and to exclude any patients prescribed for pain/analgesia.

AMENDMENT 9^th^ December 2015

